# Effect of immersive virtual reality-based cognitive remediation in patients with mood or psychosis spectrum disorders: study protocol for a randomized, controlled, double-blinded trial

**DOI:** 10.1186/s13063-024-07910-7

**Published:** 2024-01-24

**Keywords:** Virtual reality, Cognition, Cognitive remediation, Depression, Bipolar disorder, Schizophrenia, Psychosis

## Abstract

**Background:**

Cognitive impairments are prevalent across mood disorders and psychosis spectrum disorders, but there is a lack of real-life-like cognitive training programmes. Fully immersive virtual reality has the potential to ensure motivating and engaging cognitive training directly relevant to patients’ daily lives. We will examine the effect of a 4-week, intensive virtual reality-based cognitive remediation programme involving daily life challenges on cognition and daily life functioning in patients with mood disorders or psychosis spectrum disorders and explore the neuronal underpinnings of potential treatment efficacy.

**Methods:**

The trial has a randomized, controlled, double-blinded, parallel-group design. We will include 66 symptomatically stable outpatients with mood disorders or psychosis spectrum disorders aged 18–55 years with objective and subjective cognitive impairment. Assessments encompassing a virtual reality test of daily life cognitive skills, neuropsychological testing, measures of daily life functioning, symptom ratings, questionnaires on subjective cognitive complaints, and quality of life are carried out at baseline, after the end of 4 weeks of treatment and at a 3-month follow-up after treatment completion. Functional magnetic resonance imaging scans are performed at baseline and at the end of treatment. The primary outcome is a broad cognitive composite score comprising five subtasks on a novel ecologically valid virtual reality test of daily life cognitive functions. Two complete data sets for 54 patients will provide a power of 80% to detect a clinically relevant between-group difference in the primary outcome. Behavioural data will be analysed using linear mixed models in SPSS, while MRI data will be analysed with the FMRIB Expert Analysis Tool (FEAT). Treatment-related changes in neural activity from baseline to end of treatment will be investigated for the dorsal prefrontal cortex and hippocampus as the regions of interest.

**Discussion:**

The results will provide insight into whether virtual reality-based cognitive remediation has beneficial effects on cognition and functioning in symptomatically stable patients with mood disorders or psychosis spectrum disorders, which can aid future treatment development.

**Trial registration:**

ClinicalTrials.gov NCT06038955. Registered on September 15, 2023.

**Supplementary Information:**

The online version contains supplementary material available at 10.1186/s13063-024-07910-7.

## Background

Moderate-to-severe cognitive impairments are common across mood disorders (MD) and psychosis spectrum disorders (PSD) [1–3] with studies suggesting a prevalence of approximately 50% in remitted patients with major depressive disorder [4], 50–70% in remitted patients with bipolar disorder [5, 6], and up to 80% in patients with schizophrenia [7, 8]. Importantly, the impairments often persist during asymptomatic phases of illness [2, 4, 5] and are directly associated with poorer prognosis, increased functional disability, and reduced work capacity [9–12], with the latter comprising the largest socioeconomic burden of the disorders [13, 14]. The impact of cognitive impairments on functional ability highlights the need for novel therapies to not only enhance cognition but also improve daily life functioning [6, 15, 16]. Cognitive remediation (CR) is an umbrella term for therapeutic interventions that focus on ameliorating cognitive impairments through cognitive training, cognitive rehabilitation, and cognitive stimulation [16–18]. CR with a focus on cognitive training is a particularly promising approach with well-established effects on cognitive and functional outcomes in PSD [19, 20] and, more recently, findings of moderate benefits in cognitive function in MD [18, 21].

WHO’s International Classification of Functioning, Disability and Health (ICF) [22] provides a useful framework for distinguishing between cognitive *functions* such as memory or attention (i.e. the ICF level of body functions) and cognitive *skills* necessary for carrying out daily life tasks (i.e. the ICF level of activity/participation). Cognitive training in CR interventions typically targets both of these levels, aiming to normalize cognitive *functions* through ‘drill-and-practice’-based approaches, such as computer-based exercises, and improving cognitive *skills* by teaching patients to apply the cognitive gains in daily life and practicing compensatory strategies that aid daily life activities [16, 23, 24]. A strategy-based approach focusing on training cognitive skills has been demonstrated to be particularly important for increasing the transfer effects of cognitive improvement to functional outcomes in patients’ daily lives [16, 24]. Nevertheless, most CR interventions still find *limited transfer* of acquired cognitive skills to daily life functioning, which puts into question the clinical impact of the interventions [18, 20, 24]. Several challenges may contribute to the limited transfer effect. First, cognitive training rarely involves the possibility of *directly* training cognitive skills within actual challenging real-life situations, and it seems insufficient to merely discuss with patients in the therapy sessions how strategies can be applied in daily life [21, 24, 25]. Indeed, meta-analytic evidence from CR trials in PSD suggests that transfer is greater when CR is combined with more structured psychosocial rehabilitation such as vocational training [26]. Second, treatment effects in CR programmes are often also limited by difficulty in sufficiently motivating participants to complete the cognitive training despite therapist encouragement and support [27]. It has been suggested that participants may lose interest in the training, perhaps because the relatively abstract computer exercises or strategy discussions do not directly relate to their daily life cognitive challenges and therefore do not seem directly relevant [24, 28]. As such, some programmes suffer from poor treatment adherence, and attrition rates as high as 50% have been reported [21, 27, 29]. Together, these challenges emphasize the need for developing and integrating more ecologically valid and engaging techniques in CR interventions to aid transfer and treatment adherence [17, 21, 24].

Virtual reality (VR) platforms have the potential to overcome these challenges because of their highly engaging and real-life-like format. In VR, users can be immersed in naturalistic and multimodal simulations of cognitively challenging daily life scenarios that are quite like situations that patients may encounter in their daily lives [30–33]. VR thereby provides an ecologically valid method for directly practicing the cognitive strategies that are discussed in therapy in a real-life-like safe setting. Notably, studies of VR and learning have found that fully immersive VR, such as a head mounted display (HMD), has a better effect on learning performance than non-immersive learning approaches and improves knowledge transfer to solve real-world tasks [34–36]. It therefore seems reasonable to assume that VR can enhance bridging between cognitive training and daily life cognitive skills in CR interventions and facilitate greater transfer effects [33]. VR simulations using HMDs also induce an increased feeling of being ‘present’ in the virtual environment by effectively shutting out the physical reality [37, 38]. In educational contexts, an increased feeling of ‘presence’ has been shown to influence engagement in VR users by boosting interest and motivation [39]. Similar effects in CR programmes using gamified VR platforms could help instil greater motivation in patients and increase treatment adherence. A recent systematic review found initial promising evidence for the use of fully immersive VR-based cognitive training in neuropsychiatric disorders, particularly if training is relevant for daily life challenges [40]. However, cognitive intervention studies in MD and PSD using VR are still scarce and suffer from various methodological challenges, including a lack of active control groups, small sample sizes, and poor descriptions of intervention components [40–43]. To address this gap, our research group developed a fully immersive VR prototype training scenario in a virtual kitchen environment with input from individuals with MD or PSD in line with recommendations to include expert-by-experience knowledge [44, 45]. We then conducted a randomized, controlled proof-of-concept study in 40 participants with MD or PSD in which the active group trained various cognitive strategies in the VR protype training scenario [44]. This study demonstrated that short-term (1 week), intensive VR-based cognition training had the potential to improve some aspects of cognitive performance [44]. Participants also rated the VR prototype scenario as being a fun, engaging, and safe training environment that felt relevant for their daily lives [44].

A general methodological challenge in developing treatments targeting cognition is the lack of insight into the neurocircuitry targets of pro-cognitive interventions [46]. Therefore, recent recommendations by the International Society for Bipolar Disorder (ISBD) Targeting Cognition Task Force underscore the need for implementation of neuroimaging in cognitive intervention trials to increase insight into brain-based mechanisms for treatment effects [47]. A recent systematic review of studies using functional MRI found that mood disorders (MD) are consistently associated with abnormal (primarily hypo-) activity in the dorsal prefrontal cortex (dPFC) and hyperactivity in the default mode network (DMN) during working memory and strategic encoding [48]. Hypoactivity in the dPFC is also a consistent finding in patients with PSD [49]. There is growing evidence for treatment-related changes in dPFC activity following CR interventions across MD and PSD [50–52]. In keeping with this, a meta-analysis of changes in brain activity following CR in PSD found increased activity in the dPFC to be the most robust brain-based marker for cognitive improvement [50]. In our previous study of action-based cognitive remediation (ABCR) in MD, we found early treatment-related activity in the dPFC during working memory, which predicted improved executive functions after 10 weeks of treatment [53]. Together, these findings suggest that changes in the prefrontal cortex may be a potential biomarker for the effect of treatment across PSD and MD.

### Aims and hypothesis

This study aims to assess the effect of a 4-week, intensive VR-based cognitive remediation programme involving daily life challenges on cognition in symptomatically stable outpatients with MD or PSD. Additionally, we will investigate whether any treatment-related cognitive improvement translates into improved daily life functioning and is accompanied by a change in dorsal prefrontal activity. We hypothesize that VR-based cognitive remediation vs. a VR control treatment has a beneficial effect on cognition after 4-week treatment completion (primary outcome assessement time) measured with a novel ecologically valid VR test of daily life cognitive skills (primary outcome measure), a verbal learning and memory composite score based on a traditional neuropsychological test, and a performance-based measure of daily life functioning (secondary outcome measures). For exploratory purposes, we will examine neuronal underpinnings of treatment effects and effects on additional measures of cognition, functioning, and self-rating scales (tertiary outcomes).

## Methods

### Study design and participants

See Fig. 1 for a flow diagram of the trial. The project has a randomized, controlled, double-blinded, parallel-group design. We will include 66 trial participants with MD (unipolar — or bipolar disorder) in full or partial remission at the time of inclusion (score ≤ 14 on the Hamilton Depression Rating Scale [54] and Young Mania Rating Scale [55], respectively) or PSD (F20 spectrum) that have been assessed to be relatively symptom stable by their treating clinician upon referral to the study. Recruitment will be carried out through the Copenhagen Affective Disorder Clinic, the outpatient, early intervention clinics for psychotic disorders (OPUS), other mental health centres in the Capital Region of Denmark, and through advertisements on relevant websites.

**Fig. 1 Fig1:**
[figure not shown]
Flow chart of the study design

Eligible participants must be between 18 and 55 years of age, be fluent in Danish, and have an ICD-10 diagnosis of unipolar disorder (F32–F33), manic episode or bipolar disorder (F30–F31), or a psychosis spectrum disorder (F20–F29) confirmed using the Schedules for Clinical Assessment in Neuropsychiatry (SCAN) interview [56] and present with both *objective* and *subjective* cognitive impairment in line with expert recommendations [47]. *Objective* cognitive impairment is assessed with the Screen for Cognitive Impairment in Psychiatry-Danish version (SCIP-D) [57] and is defined as a SCIP total score ≥ 0.5 standard deviation (SD) below the expected total score based on age, education, and gender or as a score ≥ 0.5 SD below the expected score on a minimum of two out of the five subtests (verbal learning test—immediate, working memory test, verbal fluency test, verbal learning, test—delayed, and processing speed test) [58]. *Subjective* cognitive impairment is assessed with the Cognitive Complaints in Bipolar Disorder Rating Scale (COBRA) [59] and is defined as a score ≥ 14 [59, 60]. To ensure participant motivation, *subjective* cognitive impairment is also assessed with the Cognitive Difficulties in Everyday Life (CODEL) questionnaire, which has been developed in house to specifically assess cognitive complaints within the challenging daily life situations that are targeted by the VR intervention (see details under ‘intervention’). On the CODEL, *subjective* impairment is defined as a score ≥ 7 in a minimum of two of the four subdomains on the questionnaire (i.e. cooking, shopping, remembering verbal information, and planning). Exclusion criteria are current drug or substance abuse, a daily use of benzodiazepines > 22.5-mg oxazepam or > 7.5-mg diazepam (cut-offs for doses with limited cognitive side effects), comorbid neurological disorder or previous serious head trauma, dyslexia, pregnancy, claustrophobia, having a pacemaker or other metal implants inside the body, and electroconvulsive therapy in the 3 months prior to inclusion. All participants must provide written informed consent. The SPIRIT reporting guidelines were used for the current study [61]. See Appendix A for a completed SPIRIT checklist.

### Procedure

Upon their first visit at the Copenhagen Affective Disorder Research Centre (CADIC) or Department of Psychology, University of Copenhagen, participants are informed about the project and provide written informed consent, after which they undergo an eligibility assessment. The first author is responsible for recruitment and conducting the first visit during which the informed consent is obtained. After inclusion, the baseline assessments are scheduled and completed over 2 days, 1 to 5 days apart for practical reasons and to avoid attrition.

On day 1, the participant is assessed with a novel VR cognition test of daily life cognitive skills and a comprehensive neuropsychological test battery (see details under ‘Outcome measures’). Participants also complete questionnaires concerning subjective cognitive complaints, quality of life, and general acceptance of VR technology. Daily life functioning is assessed using a clinician-rated interview and a performance-based assessment. Participants with MD undergo mood ratings with the HDRS-17 and YMRS. For participants with PSD, positive symptoms are assessed using the Scale for the Assessment of Positive Symptoms (SAPS) [62], and negative symptoms are assessed using the Brief Negative Symptom Scale (BNSS) [63]. Finally, self-reported sleep quantity and quality in the past 3 days are recorded. At the Copenhagen University Hospital, Rigshospitalet, participants then undergo a functional magnetic resonance imaging (fMRI) scan encompassing a spatial working memory N-back task, a word encoding paradigm in which participants must encode and subsequently recognize words of typical household items, a resting state, and a structural scan.

On day 2, participants’ ability to perform daily life tasks is assessed with the Assessment of Motor and Process Skills (AMPS) [55] by an AMPS-certified occupational therapist in a standardized test kitchen.

The VR cognition test, neuropsychological assessments, questionnaires, clinical symptom ratings, assessments of functioning (including AMPS), and fMRI scan are repeated within 2 weeks after treatment completion (primary outcome assessment time). All assessments except for the fMRI scan are repeated 3 months after treatment completion to assess durability.

Participants are requested to avoid significant changes to the dose and type of any medication prior to or during the study. Any changes in the type or dose of medication will be recorded at treatment completion and at the 3-month follow-up. Patients are not excluded from the project if their symptoms worsen unless they are incapable of engaging in the treatment or voluntarily decide to drop out.

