### Randomization and blinding

The study has a double-blinded design. Neither the participant nor the outcome assessors will know whether the participant is receiving VR-based cognitive remediation or VR control treatment (details below). At inclusion, participants are informed that they will be randomized to one of two types of VR training programmes which both involve weekly sessions with a therapist. To uphold the blinding, participants are not provided with any further details regarding the VR-based cognitive remediation and control treatment until after randomization. Participants are randomized upon full completion of the baseline assessment with allocation being carried out by the first author using the automated randomization module in the online Research Electronic Data Capture (REDcap) system based on an uploaded blocked randomization list created online using Sealed Envelope Ltd. 2022 [64]. Participants will be randomized using a 1:1 allocation in blocks of varying size from 4-8, and we will stratify randomization with age (< or ≥ 35 years) and diagnosis (MD vs. PSD) to ensure equal distribution in the two groups. To avoid any predictability in the randomization process, the list detailing the randomized blocking sequences is kept inaccessible to the first author who enroll and randomize the participants. The participants will be instructed not to disclose any information concerning their treatment during outcome assessments and under no circumstances will the allocation be revealed to the outcome assessors. Outcome assessors will be asked to note whether the blinding was compromised during the assessment. The first author who undertakes the statistical analyses will be blinded with respect to group assignments when conducting the primary and secondary outcome analyses.

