**Fig. 2 Fig2:**
[figure not shown]
Virtual reality training environments

The virtual reality training is supported by a psychoeducational programme that focuses on the application of learned cognitive strategies in daily life. The programme is designed to match the content of the weekly VR training scenario and covers the following themes: meta-cognition and seeking out cognitive challenges (week 1), strategic learning and memory strategies (week 2), verbal memory and sustaining attention (week 3), and organizing and prioritizing (week 4). The first session also introduces the structure of the treatment and focuses on individual goal setting, including identification of cognitive strengths and weaknesses based on the screening carried out during the eligibility assessment. Each session consists of a short presentation of the theme of the day followed by training in VR (2 × 30 min) and a discussion of how the VR training is related to the individual experiences and goals of the participant. Each session ends with identifying cognitively challenging tasks for the participant to carry out between sessions (e.g. cooking a meal, going shopping without a list, remembering conversation, reading, or organizing and completing tasks at home). Participants then take a head-mounted display (HMD) home to conduct between-sessions VR training (2 × 30 min of home training per week). Treatment completion is defined as 80% attendance corresponding to full completion of six out of eight in-person training sessions. When a participant is unable to attend a scheduled session, the therapist will help the participant catch up on the session’s content through additional at-home training or by extending the subsequent treatment session. The VR training at home is recorded for subsequent evaluation of feasibility. At the final session, participants return the HMD, and a discussion takes place on whether and how they benefited from the intervention, along with encouraging them to keep practicing learned skills. They also receive a leaflet with information from the training sessions.

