### Statistical considerations

#### Primary, secondary and tertiary outcome analyses

To investigate the effect on cognition of VR-based cognitive remediation, data will be analysed using linear mixed models for both primary and secondary outcome measures using the Statistical Package for the Social Sciences (SPSS) version 28. For the primary outcome measure, the dependent variable will be the CAVIR cognitive composite score, which is derived by averaging the five z-transformed subtest scores [69]. Data for neuropsychological tests, level of functioning, subjective cognition, and quality of life will also be analysed using mixed models. Intention-to-treat (ITT) analyses will be performed for missing data using a mixed models approach without any ad hoc imputation [88]. Data will be analysed for every randomized participant for all assessments. Interim analyses will not be conducted given the study’s nature and scale.

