#### Data management and monitoring

All personal information will be obtained at the eligibility assessment or from patient records in cases where participants are unable to provide the needed information. Pseudo-anonymized data from the neuropsychological tests, virtual reality test, questionnaires, interviews, and functional assessment will be registered in the REDcap database, which meets requirements from the Danish Data Protection Agency. Data quality is ensured by score range restrictions on values for all outcomes, and all data for the primary and secondary outcome measures will be double-checked by the first author. Signed consent forms as well as a list that matches participant ID numbers with personal information are kept separate from pseudoanonymized data. The list matching participants’ personal information with their ID number will be deleted and consent forms maculated 10 years after study completion. At this point, all data will be completely anonymized. All trial authors will have access to the final trial data set. If a participant is excluded from or withdraws from the study, the reason for exclusion will be documented in REDcap, along with information regarding any adverse events.

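### Staying in the project is tied to being able to engage in treatment after randomisation, which fits poorly with the intention-to-treat analysis and risks informative loss of outcomes

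*Protocol article*

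**What the plan says.** Five places in the protocol article bear on this.

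- **Procedure (medication and worsening).** Patients whose symptoms worsen stay in the project "unless they are incapable of engaging in the treatment or voluntarily decide to drop out". The sentence concerns exclusion from the project, not from the treatment.
- **Randomization and blinding.** "Participants are randomized upon full completion of the baseline assessment". Treatment follows, so inability to engage in it can only arise after randomisation.
- **Data management and monitoring.** "If a participant is excluded from or withdraws from the study, the reason for exclusion will be documented in REDcap", together with any adverse events. Exclusion and withdrawal are named as two separate events. Nothing is said about further outcome assessment after either.
- **Primary, secondary and tertiary outcome analyses.** "Intention-to-treat (ITT) analyses will be performed for missing data using a mixed models approach without any ad hoc imputation", followed by "Data will be analysed for every randomized participant for all assessments".
- **Procedure and Intervention (timing).** The end-of-treatment assessments "are repeated within 2 weeks after treatment completion (primary outcome assessment time"), and the follow-up comes 3 months after completion. Completion itself is an attendance count: "Treatment completion is defined as 80% attendance corresponding to full completion of six out of eight in-person training sessions".

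**The concern.** Intention-to-treat needs outcomes from people who stop treatment as well as from those who finish. Here, a participant who worsens to the point of being unable to engage leaves the project, and on the plain reading the later assessments then do not take place. No analysis method can recover outcomes that were never collected.

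The missing outcomes would not be a random subset. The trigger is clinical deterioration after the last recorded score, and deterioration is likely to go with poorer cognition and functioning. A mixed model without imputation is valid if data are missing at random given what was observed. For these participants, usually only the baseline score was observed.

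The loss could also be unequal. The active programme asks for more time, so the same patient might be unable to engage in one arm and able in the other. The estimate would then move from the effect in everyone randomised towards the effect in those able to train.

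**Working it through.** **1. Set the passages side by side.** Randomisation follows baseline, treatment follows randomisation, and inability to engage in treatment (after worsening) is a ground for leaving the project. Data management lists exclusion separately from withdrawal and mentions only recording the reason and adverse events. Both later assessments are dated from treatment completion, so someone who stops early has no stated date for either visit. The analysis section includes everyone randomised and foresees missing data. The text is therefore consistent about who is analysed. The weak point is whether any post-baseline data would exist for the excluded.

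**2. What the mixed model does with them.** Their baseline score keeps them in the data set. Baseline alone says almost nothing about the treatment contrast, so under missing at random the estimate is close to the effect in those retained.

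**3. Scheduled load by arm** (Intervention and Virtual reality control treatment sections).
- Active: 2 sessions × 2 h × 4 weeks = 16 h, plus home training 2 × 0.5 h × 4 weeks = 4 h. Total 20 h, before homework tasks.
- Control: 1 session × 2 h × 4 weeks = 8 h.
- Ratio: 20/8 = 2.5.

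**4. The plan's own loss figure** (Sample size and power calculation). 66 recruited for 54 complete gives 12/66 = 18.2%, which the article calls approximately 20%. Per arm this is 33 − 27 = 6. It covers drop-out from all causes. No figure is given for exclusions under the Procedure rule.

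**5. Illustration of size.** Inputs: 33 per arm and a 0.60 z difference in change (both from the sample size section). Assumptions: k active participants are excluded under this rule, they would have gained nothing over control, the control arm loses nobody this way, and the model reports the effect in those retained.

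All-randomised effect = 0.60 × (33 − k)/33.

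| k of 33 | All-randomised effect (z) | Overstatement (z) |
|---|---|---|
| 1 | 0.60 × 32/33 = 0.58 | 0.02 |
| 2 | 0.60 × 31/33 = 0.56 | 0.04 |
| 3 | 0.60 × 30/33 = 0.55 | 0.05 |
| 6 | 0.60 × 27/33 = 0.49 | 0.11 |

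The last row is a ceiling: it spends the whole loss allowed for in one arm on this single rule. If the excluded fall short of the rest by 0.3 to 0.9 z rather than by 0.60 z, the overstatement is (k/33) × gap, from 1/33 × 0.3 = 0.01 z to 6/33 × 0.9 = 0.16 z.

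**The case against.** The strongest reply is that the Procedure sentence is mainly protective. By default, patients who worsen are kept, and only worsening together with inability to engage, or a voluntary decision to leave, ends participation. Voluntary withdrawal is ordinary in any trial. Missed sessions can be caught up, the six-of-eight rule defines completion and not exclusion, and there are retention measures. Participants are selected as symptomatically stable and treatment lasts 4 weeks, so exclusions under this rule may be few. All of this stands, and it limits the size of the problem.

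It also stands that the analysis section promises analysis, not complete data. A reader might infer that the plan contradicts itself outright, or that treatment failures are removed from the outcome data. The documents do not support that. No passage says that collected data are deleted, that excluded participants leave the analysis set, or in so many words that their assessments stop. The last is the plain reading of exclusion from the project, but it is a reading.

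It may further be said that follow-up after stopping treatment is a detail an article leaves to the full protocol. That would hold if the article were silent. It is not: it states a rule, and the rule attaches to the project. An analysis plan that is not shown could not repair this, because the matter is data collection.

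**Conclusion.** The point holds as a poorly fixed rule. As written, remaining in the project depends on ability to engage in treatment after randomisation, and this undercuts the intention-to-treat aim. Missing at random is doubtful for those affected. A difference between arms is possible given the unequal load, though no passage links load to exclusion.

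The size is unknown. Under the assumptions above, 1 to 6 exclusions among 33 active participants put the all-randomised effect at about 0.58 to 0.49 z against a reported 0.60 z, with small numbers more likely than the ceiling. A reader might take the planned 20% loss and conclude that the effect is overstated by a quarter: 0.80 × 0.60 = 0.48, and 0.60/0.48 = 1.25. That is not supported. The 20% is drop-out from every cause, including voluntary withdrawal, and should not be assigned to this rule. Zero benefit in everyone lost is an assumption too. If exclusions were similar in both arms, much of the bias could cancel.

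The change is worth making because it is cheap and protects the primary comparison, not because a large bias has been shown.

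**What to change.** Reconcile the Procedure, Data management and outcome-analysis sections by separating stopping treatment from leaving the study:

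- Every randomised participant, whatever their engagement or clinical course, is invited to the end-of-treatment and 3-month assessments unless consent is withdrawn.
- For those who stop early, the visits are dated by the planned calendar time, that is, from the scheduled end of the 4-week programme.
- If the full visit is refused, at least the CAVIR test (primary outcome) and the RAVLT (key secondary cognitive outcome) are offered.
- These data enter the primary mixed model.
- Stopping treatment and leaving the study are recorded as separate events, with reasons, by arm.

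The decision to stop treatment is left unchanged. The cost is a few sentences of text and a few already planned visits for participants who stop treatment, some of whom may decline. With 35 of 66 included by September 2023, the remaining 31 could still benefit, as could any earlier participants whose later visits were outstanding.
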